### Participant timeline {13}

The maximum study duration (i.e. starting at enrolment and ending at close-out) for a given patient is 15.5 months. The anticipated study calendar provides for 12 months of inclusion, 15 months of follow-up, 6 months of data management and 6 months of statistical analysis and report writing. The time from inclusion to randomization should not exceed 3 months (see Fig. 1).

**Fig. 1 Fig1:**
[figure not shown]
Schedule of enrolment, interventions and assessments according to the Standard Protocol Items: Recommendations for Intervention Trials (SPIRIT) Diagram

### Sample size {14}

We will test the following hypothesis: The mean time to the next suicide attempt during the follow-up period is different between the two groups. The probability of a suicide reattempt-free follow-up period (PSRFFP) according to usual care was estimated at 60% by Brown et al. [6]. In this trial, a cognitive behavioural therapy (10 sessions of individual therapy) was associated with an increase of 20% in the PSRFFP at 12 months.

In our study, the 10 sessions of individual therapy program are replaced by 6 sessions of a group therapy program. We expect a minimum benefit of 20% for this new strategy (60% in the control group versus 80% in the experimental group).

To our knowledge, no study has reported intra-class correlation coefficients associated with therapists or group therapy suicide re-attempt of the C-SSRS score. It is therefore difficult to anticipate an exact sample size that would take into account clustering effects caused by group therapy (or by therapist effects) in the primary outcome assessment.

Under the hypothesis of no cluster effects (at either the therapist or therapy-group levels) and using a log-rank test, 186 subjects are required to detect 20% difference in PSRFFP at 12 months (60% in the control group and 80% in the experimental group), with a power of 85% and a bilateral alpha risk of 5%.

Given the possibility of cluster effects, we have increased this number to 216. Taking into account an anticipated rate of 10% lost to follow-up, 240 patients will be included (120 patients per group).

Patient consulting under emergencies for suicidal behaviour are common. It is more than reasonable to expect at least one case per day per centre on average, giving a minimum potential patient pool of about 1460 patients during the proposed recruitment period. To take into account the time necessary to organize group sessions and the probability that some patients might not want to participate, we proposed an inclusion averaging 5 patients per month per centre.

### Recruitment {15}

Recruitment will be carried out by the participating psychiatrists during visits with potential patients at the eight centres. It is difficult to estimate the available patient pool via hospital statistics because suicide ideation is not coded. However, patients consulting under emergency situations for suicidal behaviour are common (there are over 800 hospitalizations for suicide attempts at the NUH per year). It is more than reasonable to expect at least one case per day per centre on average, giving a minimum potential patient pool of about 1460 patients during the proposed recruitment period. Recruitment of patients started in November 2017 and will be completed in June 2021. The first groups, one that started with GCBT and the other with IST, received treatment from December 2017 to January 2018. In order to take into account the time necessary to organize group sessions and the probability that some patients might not want to participate, we propose an inclusion curve averaging 5 patients per month per centre.

### Assignment of interventions: allocation

#### Sequence generation {16a}

Patients will be randomized to either study arm in a 1:1 ratio. Randomization lists consisting of randomly sized blocks will be established per centre. These lists are the responsibility of the study methodologist at the Department of Biostatistics, Epidemiology, Public Health and Medical Information at the Nîmes University Hospital (BESPIM). A specifically designed SAS program (Cary, NC, USA) will be used to carry out randomization. The number of subjects per block will be known only to the methodologist.

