## Methods, participants, interventions and outcomes

### Study setting {9}

The clinical aspects of this trial will take place within participating academic or private hospitals (urban setting) located in France. Eight centres (seven academics and one private) have agreed to participate. The list of study site could be obtained by contacting the sponsor.

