The Columbia Suicide Severity Rating Scale (C-SSRS). This physician-administered scale prospectively measures the severity and intensity of suicidal ideation, the different types of suicidal behaviour and the lethality of suicide attempts [15]The Beck Scale for Suicide Ideation (BSSI) is a 21-item, validated, self-report questionnaire that can be used to identify the presence and severity of suicidal ideation [16, 17]The Beck Depression Inventory (BDI-II) is a self-assessment scale. Its purpose is to quantify the intensity of depression [18]The Beck Hopelessness Scale (BHS) is a validated questionnaire designed to measure an individual’s expectations about the future [19]The Mini International Neuropsychiatric Interview – 7 (MINI) is a tool that helps identify the psychopathology of a subject according to the DSM5 [20]The Risk-Rescue Rating Scale (RRRS) assesses the lethality of a suicide attempt, defined as the probability of inflicting irreversible damage. The underlying hypothesis is that lethality can be expressed as a ratio of factors influencing risk and rescue [21]Demographic forms and other assessments are used to characterize the sample and control for potential confounders.These additional scales provide valid appraisals of factors related to suicidal behavior such as:Life events: the Social Readjustment Rating Scale (SRRS [22];), the Childhood Experience of Care and Abuse Questionnaire (CECA-Q [23];)Personality traits: Spielberger’s State-Trait Anger Expression Inventory (STAXI-2 [24];), Barratt Impulsiveness Scale (BIS11 [25];), State-Trait Anxiety Inventory (STAI [25];)Cognitive functioning: the Cognitive Reflection Test (MIT-IQ [26];)Severity of alcohol and tobacco dependence: the CAGE Questionnaire [27] and the Fagerström questionnaires [28]

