##### Analysis of the principal endpoints

The duration of a suicide reattempt-free follow-up period (SRFFP) will be assessed in the two groups using the Kaplan-Meier method and compared by a log-rank test. This analysis will be completed by a modeling analysis to take into account clustering effects.

Indeed, in our study, randomization to treatment is done on an individual basis. However, the experimental treatment is administered to a group so that several individuals receive the intervention together by the same therapist. Observations within the group therapy will likely be correlated within groups (clustering effect). In contrast, control participants receive an individual intervention and their observations can reasonably be assumed to be independent. Either arm may also be influenced by cluster effects linked to a particular therapist. The latter clustering results in asymmetric, partially nested designs. Recently, statistical models were developed to appropriately evaluate treatment effects when using a partially nested design [29]. Based on these, we will use multilevel mixed-effects models to assess the treatment effect on the outcomes describing the suicidality:
The duration of a suicide reattempt-free follow-up period (SRFFP),The suicide reattempt during the follow-up (yes/no) by adjusting for nested effects,The C-SSRS score at 12 months by adjusting for nested effects and C-SSRS score at inclusion.

The detailed statistical plan will be provided before data extraction and unblinding.

The models will also provide valuable estimates of intracluster correlation coefficients for the different psychological outcomes of our study in the context of behavioural group therapy; these data are necessary to optimize the sample size of further studies in the area of psychological research.

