#### Methods for any additional analyses (e.g., subgroup and adjusted analyses) {20b}

Additional analyses are not required.

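### Randomisation is stratified by centre, but no stated analysis uses centre and baseline adjustment is stated for one outcome only: a cheap, modest gain in efficiency is left unused

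*Protocol article*

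**What the plan says.** Sequence generation {16a} sets 1:1 allocation and states: "Randomization lists consisting of randomly sized blocks will be established per centre". Study setting {9} gives the number of strata: "Eight centres (seven academics and one private) have agreed to participate".

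Under Analysis of the principal endpoints, reattempt-free time "will be assessed in the two groups using the Kaplan-Meier method and compared by a log-rank test". No stratum or covariate is named. The section continues: "This analysis will be completed by a modeling analysis to take into account clustering effects". The levels it goes on to describe are the therapy group in the experimental arm and the therapist: "Either arm may also be influenced by cluster effects linked to a particular therapist". Centre is not named there or under Analysis of the secondary endpoints.

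Only one model has a stated baseline covariate: "The C-SSRS score at 12 months by adjusting for nested effects and C-SSRS score at inclusion". The secondary-endpoint section models how C-SSRS, BSSI, BDI-II and BHS evolve, without saying how the baseline value enters.

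Two statements bear on adjustment in general. Outcomes {12} says: "Demographic forms and other assessments are used to characterize the sample and control for potential confounders". Section {20b}, whose heading gives subgroup and adjusted analyses as its examples, says: "Additional analyses are not required".

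**The concern.** When allocation is balanced within centres, the between-centre part of the outcome variation is removed from the treatment contrast by design. An analysis that ignores centre still counts that part as noise. If centres differ in reattempt risk, the test then rejects less often than its nominal level allows, and some power is given up.

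The same holds for baseline severity. The C-SSRS is recorded at inclusion and questionnaires are given at baseline. If any of these scores predicts reattempt, leaving it out of the model for reattempt-free time forgoes precision that costs nothing to obtain.

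The two general statements also leave it unclear what adjustment is intended. One gives confounder control as a purpose of the assessments. The other asks for nothing further under a heading that covers adjustment. Covariates should be fixed before the arms are revealed, so this should be settled early.

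**Working it through.** **Inputs from the document.** Eight centres, 1:1 blocked allocation within centre; 60% versus 80% reattempt-free at 12 months; 85% power; two-sided 5%; N = 186 before inflation, 216 after the cluster allowance, 240 after 10% loss (Sample size {14}).

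**Inputs assumed.** The between-centre SD of the log-hazard (0 to 0.7) and the hazard ratio per SD of one baseline score (1.0, 1.5, 2.0). The document gives neither.

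**The plan's own figure.** Two proportions with pooled variance, per arm:

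n = [1.96·√(2·0.7·0.3) + 1.036·√(0.6·0.4 + 0.8·0.2)]² / 0.20² = (1.270 + 0.655)² / 0.04 ≈ 92.7, so 93 per arm and 186 in total. Then 216 / 0.90 = 240. Both match. No stated figure is in dispute.

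**Effect size.** Under proportional hazards, 60% versus 80% gives HR = ln 0.8 / ln 0.6 = 0.437.

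**Simulation.** 6,000 trials per setting, N = 216, eight equal centres, blocked allocation within centre, exponential times censored at 12 months. The marginal rates are held at 60% and 80% in every setting, so that changing the centre variance does not change the effect being tested. There is no therapy-group clustering.

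| Centre SD | Score HR per SD | Power: unstratified log-rank | Power: stratified log-rank | Power: Cox, stratified and adjusted | Type I: unstratified | Type I: stratified log-rank |
|---|---|---|---|---|---|---|
| 0 | 1.0 | 90.9% | 90.4% | 90.0% | 5.0% | 5.0% |
| 0.3 | 1.0 | 90.7% | 91.0% | 90.4% | 4.5% | 4.9% |
| 0.6 | 1.0 | 91.2% | 92.8% | 92.4% | 3.8% | 4.8% |
| 0 | 1.5 | 91.2% | 90.9% | 91.5% | 5.2% | 5.0% |
| 0 | 2.0 | 91.4% | 91.3% | 93.8% | 5.2% | 5.1% |
| 0.3 | 1.5 | 90.9% | 91.2% | 92.0% | 4.2% | 4.3% |
| 0.6 | 2.0 | 91.0% | 92.3% | 95.3% | 4.1% | 5.0% |

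Simulation standard error: √(0.91·0.09/6000) ≈ 0.4 points for power and √(0.05·0.95/6000) ≈ 0.3 points for type I error.

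- Stratifying alone: from 90.4 − 90.9 = −0.5 to 92.8 − 91.2 = +1.6 points.
- Stratifying and adjusting: from 90.0 − 90.9 = −0.9 to 95.3 − 91.0 = +4.3 points.

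**Check at the enrolled size.** N = 240 with 10% dropout, 3,000 trials per setting, same marginal rates, unstratified versus stratified: SD 0, 91.9% v 91.4%; SD 0.3, 91.4% v 92.0%; SD 0.5, 92.2% v 93.0%; SD 0.7, 92.4% v 94.0%. A further run at this size gave −0.4 to +1.9 points, with unstratified type I error of about 3.9% at SD 0.5 to 0.7.

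**The case against.** The strongest reply is that this is an article and that it promises a fuller statistical plan before the data are extracted and the arms revealed. Strata and covariate lists usually belong there, and the text says only that a log-rank test is used, not that it is unstratified. This stands in part: that plan may already contain the remedy. But the article does describe its models level by level without centre, and its two statements on adjustment pull in different directions. Stratifying by the randomisation factor is a better method than the one written, whatever is added later.

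Four stronger readings are tempting and are not supported.

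- **That adjusted analyses are ruled out.** The word stands only in the heading of {20b}. The sentence can mean that nothing is needed beyond what is already listed, and that list includes adjustment for C-SSRS at inclusion. This is a tension in wording, not a prohibition.
- **That centre and baseline are ignored throughout.** Interventions description {11a} says that each centre offers both therapies and each psychologist gives one. Therapist effects therefore absorb some between-centre variation in the multilevel model, though not in the log-rank test. Models of how scores evolve may also carry the baseline value as a repeated measure, although the text does not say so.
- **That the result is biased or the test invalid.** Any departure caused by centre is towards too few rejections. An unadjusted hazard ratio is a legitimate marginal quantity that differs from the adjusted one.
- **That 2 to 5 points of power are lost by not stratifying.** Such figures appear if a conditional hazard ratio of about 0.5 is assumed (82% v 84% at SD 0.5; 79% v 84% at SD 0.7). The protocol's rates imply 0.437. With the marginal rates held at 60% and 80%, the gain is at most about 2 points.

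**Conclusion.** The point holds as a modest improvement. The stated analysis does not reflect the stratified allocation, baseline adjustment is stated for one outcome only, and {20b} and Outcomes {12} need reconciling. The consequence is mild conservatism and possible lost efficiency.

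At the protocol's own rates, stratifying by centre is worth about −0.5 to +2 points of power. Stratifying and adjusting for one baseline score is worth about −1 to +4. The upper end needs a strongly prognostic score, with a hazard ratio of about 2 per SD. With no centre effect and an uninformative score there is nothing to gain.

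These figures assume equal centre sizes, exponential times and no therapy-group clustering. The baseline power of about 91% is therefore optimistic, since the protocol expects possible clustering and says that it cannot size it. Stratifying by centre does not deal with therapy-group clustering, which remains the task of the multilevel model.

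**What to change.** 1. Keep the log-rank test as the primary test, and stratify it by centre.
2. Include centre as a term in the multilevel models, alongside therapy group and therapist.
3. Before unblinding, prespecify one or two baseline scores already collected, for example C-SSRS or BSSI, as covariates in the model for reattempt-free time.
4. State that the BSSI, BDI-II and BHS models use each scale's own baseline value, and how.
5. Reword {20b} to agree with the purpose given in Outcomes {12}.

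The cost is wording only, with no new data and no change to the sample size. The downside is up to about 1 point of power if neither centre nor the chosen scores are prognostic. Because the missing-data section has no replacement method for outcomes other than the primary one, a simple rule for missing baseline values is also needed, so that covariate adjustment does not drop randomised patients from the intention-to-treat set.

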#### Concealment mechanism {16b}

A web application for patient randomization will be created for the needs of the study. Following user login, patient identification (first letter of last name + first letter of first name + year of birth) and verification of screening and exclusion criteria, the study arm will be indicated to the user. The use of a web application thus ensures a high degree of security as concerns randomization: it is impossible to modify the order of randomization; patient assignment to a study arm and a randomization number is definitive. The web application will be implemented by the e-Santé team at the BESPIM.

#### Implementation {16c}

The allocation sequence will be generated by the study methodologist at the BESPIM. Patient enrolment will be carried out by including psychiatrists. Randomization is carried out after patient inclusion and after baseline assessments by participating psychologists (i.e. not the including psychiatrists, who are also the outcome assessors).

### Assignment of interventions: blinding

#### Who will be blinded? {17a}

Baseline assessments will be made before randomization, so these are blinded. Patients cannot be blinded but will be asked to not reveal their group status to anybody outside their group, not even their treating psychiatrist. Furthermore, the hypotheses tested will not be communicated to patients (i.e. the patient will not be informed on the supposed superiority of one group over another).

Therapy care providers (psychologists) cannot be blinded. In order to make assessments as objective as possible, outcome assessors (psychiatrists) will be different from the therapy providers (psychologists), and every attempt will be made to keep outcome assessors blinded to patient group status. To control for the success of blinding, a “guess-the-group” question will be addressed to outcome assessors. Outcome assessor responses will be compared to expected results due to chance. Data analysts will not be involved in trial field logistics and will be blinded. During analyses, when group assignments are first required they will only be revealed as “group A” or “group B”. Only when analyses have been completed will the exact nature of groups be revealed.

#### Procedure for unblinding if necessary {17b}

We do not anticipate any requirement for unblinding. The exact nature of groups will be revealed only when analyses will be completed.

### Data collection and management

#### Plans for assessment and collection of outcomes {18a}

The coordinating psychologist will visit each participating center to present the interventional therapies and homogenize practice between centres. In each participating center, the psychologists will be instructed about one of the interventional therapies (GPACTS or IST) and will receive a treatment manual. This treatment manual will be used during the treatment to help the psychologists to stay focused on interventional therapies.

#### Plans to promote participant retention and complete follow-up {18b}

Upon enrolment and then randomization, patients will be provided with a study calendar and an authorized study technician will help patients organize their follow-up visits. The study technician will regularly telephone participants to remind them of upcoming visits and to perform any necessary rescheduling if possible. Patients will be asked to provide the name and contact information for a trusted person in case of loss of contact with study personnel. In case contact with the patient is lost, study technicians will contact the trusted person or the patient’s generalist in order to re-establish contact and organize study visits. A list of participants lost to follow-up or declared as deceased will be mailed to the Center for Epidemiology on Medical Causes of Death register (CépiDc) to verify the vital status and, if appropriate, the cause of death.

### Data management {19}

Data management will be performed in line with The International Conference on Harmonisation of Technical Requirements for Registration of Pharmaceuticals for Human Use (ICH) requirements. The related documents will be stored on the BESPIM server.

#### eCRF data

eCRF fields are formatted so as to enforce homogenous value types and require confirmation for less probable values and/or out-of-expected-range values: data entries, modifications, who made them and when are fully traceable (complete audit trail). An electronic signature by the investigator engages his/her responsibility for the data in an eCRF.

The eCRF will represent only raw data values as opposed to calculated values, unless the latter are necessary for further eCRF input.

#### eCRF data security

The software used to create eCRFs is hosted on a website within the Nîmes University Hospital (NUH). Access to this software is secured via a password. The data collected through generated eCRFs are subject to daily backup on a secure network. The network is connected to the Internet and the access is protected by a firewall.

Clinical study data will be stored in a specific directory on the server. Only network administrators and authorized persons from the BESPIM may have access to this directory.

The following measures were taken to implement confidentiality:
The required information technology is located in the BESPIM; access is controlled and secure.Data are stored on a server hosted in a secure room at the NUH.

To cope with any hardware or software problem that could occur involving the storage unit of virtual machines, another storage unit that is larger in terms of space, but less swift in terms of throughput, is deployed. Dedicated software (VRangerPro) provides a daily incremental backup of virtual machines (except Saturdays and Sundays). A full backup of these machines is performed every Friday night for an instant return to N-15 days in case of problems.

The hard drives of the virtual servers are installed “en raid”, which ensures IT security in case of hardware failure of one of the disks.

Clinical study data will be stored in a database server. Only network administrators and authorized BESPIM personnel can access this server.

#### eCRF extractions

The extraction of data for analysis will be conducted by authorized BESPIM personnel who possess the necessary rights in the eCRF application.

### Confidentiality {27}

The closing of the trial including the closure of the centres will be conducted in accordance with Good Clinical Practices and ICH. Medical and administrative records and CRFs will be kept for the duration of the study in the service and then archived for a minimum of 30 years. In accordance with article R.5120 of the French Public Health Code, the investigators, as well as any persons collaborating in the study, will respect medical confidentiality especially as concerns the nature of the study, the persons participating in the study and the obtained results.

On all study-related documents, the patient will be identified using only a unique, 7-character identification number, and the first letter of his/her last name, the first letter of his/her first name and his/her year of birth. A patient identification list will be maintained by the investigator (and only the investigator). The investigator will ensure that the anonymity of each person involved in the study is respected. No identifying information will be disclosed to third parties other than those statutorily entitled to hold this information (and who are bound by professional secrecy).

